## Abstract

**Background:**

The trend of increasing numbers of patients with type 2 diabetes emphasizes the need for active screening of high-risk individuals and intensive lifestyle modification (LSM).

**Methods/design:**

The community-based Korean Diabetes Prevention Study (C-KDPS) is a randomized controlled clinical trial to prevent type 2 diabetes by intensive LSM using a web-based program. The two public healthcare centers in Korea are involved, and 420 subjects are being recruited for 6 months and will be followed up for 22 months. The participants are allocated randomly to intensive LSM (18 individual sessions for 24 weeks) and usual care (control group). The major goals of the C-KDPS lifestyle intervention program are: 1) a minimum of 5–7% loss of initial body weight in 6 months and maintenance of this weight loss, 2) increased physical activity (≥ 150 min/week of moderate intensity activity), 3) balanced healthy eating, and 4) quitting smoking and alcohol with stress management. The web-based program includes education contents, video files, visit schedules, and inter-communicable keeping track sites. Primary outcomes are the diagnoses of newly developed diabetes. A 75-g oral glucose tolerance test with hemoglobin A1c level determination and cardiovascular risk factor assessment is scheduled at 6, 12, 18, and 22 months.

**Discussion:**

Active screening of high-risk individuals and an effective LSM program are an essential prerequisite for successful diabetes prevention. We hope that our C-KDPS program can reduce the incidence of newly developed type 2 diabetes and be implemented throughout the country, merging community-based public healthcare resources and a web-based system.

**Trial registration:**

Clinical Research Information Service (CRIS), Republic of Korea (No. KCT0001981). Date of registration; July 28, 2016.

## Background

Type 2 diabetes, with its accompanying complications, is an enormous health burden worldwide. The cost related to diabetes was U.S. $245 billion in 2012 in the U.S., and U.S. $ 673 billion in 2015, representing about 11% of worldwide healthcare expenditure [1, 2]. In 2013, total antidiabetic pharmacy expenditure was U.S. $4 billion (480 billion won) in Korea [3]. Moreover, the higher prevalence of prediabetes than of diabetes is a more serious health concern that requires urgent intervention. Diabetes prevention should be the first step.

Preventive effects of lifestyle intervention (LSI) with diet and exercise have been proven in adults with high risk of type 2 diabetes in several landmark randomized clinical trials (RCTs). [4]. The first RCT of LSI, the Finnish Diabetes Prevention Study (DPS), showed a 58% relative reduction in the incidence of diabetes compared to the control group [5]. In addition, sustained lifestyle changes and a reduction in type 2 diabetes incidence after 3 years of stopping LSI have been demonstrated [6]. The LSI program of the U.S. Diabetes Prevention Program (DPP) decreased the incidence of new type 2 diabetes by 58%, compared with 31% in a metformin-treated group [7]. Even during the 10 years’ follow-up since randomization to U.S. DPP (DPP Outcome Study), the diabetes incidence rate was reduced by 34% in the lifestyle group compared with placebo [8]. In the Da-Qing study, involving 577 Chinese people with impaired glucose tolerance, the risk of type 2 diabetes was reduced by 31% with diet, 46% with exercise, and 42% with diet plus exercise [9]. Therefore, LSI is a powerful and long-term strategy to prevent type 2 diabetes.

However, a diabetes prevention trial conducted in a community is inadequate. The Reaching Out to Prevent Increases in Diabetes (RAPID) study was a randomized effectiveness trial designed to evaluate the weight loss effectiveness of a YMCA model for the DPP intervention [10]. This YMCA model for translating the DPP intervention achieved significant weight loss at 12 months among low-income adults [10]. In addition, several countries tried to implement type 2 diabetes prevention actions in public health or clinical care [11–15]. These studies have shown that diabetes is preventable, and population-level approaches are needed for widespread implementation [16]. To do this, a careful and thorough review is needed for selection of target population and resources; establishment of appropriate target goals; determination of intervention modality, mode of delivery, and feasibility of the intervention program; and consideration of cultural differences, and so on [16, 17].

Korea has a national health screening examination service, provided by the National Health Insurance Service (NHIS) through 254 public healthcare centers across the country, and an excellent internet infrastructure. Korean people aged 40 years and older are required to undergo a mandatory health examination survey every 2 years, and the costs are covered by the NHIS in Korea [18]. In addition, the internet penetration rate of Korea is 95%, and the internet speed ranks as the first in the world. Even elderly people can use the internet and mobile devices with or without help. Therefore, the conditions are favorable both for the screening of high-risk individuals for type 2 diabetes and for internet-based LSI in Korea.

Currently, Korea has no available diabetes prevention program operated by an internet-based LSI system in the community setting, especially not in public healthcare centers run by the government. To the best of our knowledge, this is the first RCT study of a translational diabetes prevention program using a web-based system in a community setting.

## Aims

The purpose of this manuscript is to provide a detailed description of the web-based LSI program used in a community setting in the Korean Diabetes Prevention Study (KDPS).

## Methods

### C-KDPS steering committee

The community-based KDPS (C-KDPS), is an intensive LSI program that was developed by the C-KDPS steering committee from the two Diabetes Centers of the Catholic University of Korea (Seoul St. Mary’s Hospital and St. Vincent’s Hospital) and the Institute of U-Healthcare core in December 2015. The committee members are composed of the principal investigator from each clinical center, a diabetologist, a diabetes educator, a registered dietitian, exercise physiologists, and a web programmer. The C-KDPS program was based on the U.S. Diabetes Prevention Program (DPP). After an extensive literature review, the committee members developed the C-KDPS study protocol on the basis of recommendations from the SPIRIT statement on randomized trials (Table 1) [19]. The principal investigator of each center plays a role in the communications between the committee and two public healthcare centers in Chungju City and Suwon City in Korea. The committee members held regular meetings to check the process of preparing, tracking, and updating the progress on implementing the C-KDPS program in the two cities every week from December 2015. The lifestyle modification (LSM) protocol and development process was reviewed and approved by IRBs of St. Vincent’s hospital (No. VC16MISI0003) and Seoul St. Mary’s hospital (No. KC16EISI0234). This trial has been registered with the Clinical Research Information Service (CRIS), Republic of Korea (KCT0001981). This C-KDPS program protocol has also been reviewed and certified by the Korean Diabetes Association.

**Table 1 Tab1:** Proposed timeline of C-KDPS

Year	2016		2017				2018				2019
Term	3	4	1	2	3	4	1	2	3	4	1
Enrollment											
1^st^ screening	X	X									
2^nd^ screening		X	X								
Informed consent		X	X								
Allocation		X	X								
Intervention											
LSI		X	X	X	X	X	X	X	X	X	
Assessment											
6-month FU				X	X						
12-month FU						X	X				
18-month FU								X	X		
22-month FU										X	X
Web system											X

*FU* follow-up

### Study design

The Community-Based Korean Diabetes Prevention Study (C-KDPS) is a prospective RCT. A total of 420 subjects at high risk of developing type 2 diabetes will be enrolled in this study. The participants are randomly assigned either to a control group or to an intensive LSI group. Figure 1 shows the flow of participants through the study in each center.

**Fig. 1 Fig1:**
[figure not shown]
Schematic diagram of study protocol

### Randomization

In this study, a stratified blocked randomization strategy will be used to achieve between-group comparability, and to avoid imbalance in the number of subjects in each stratum. The randomization entails measuring the level of the stratified factors—center and sex—for eligible subjects, determining to which stratum each belongs, and using a block size of 4 within each stratum. Stratified blocked randomization in both centers will be conducted by study staff not involved in the intervention through a central computerized process. The sequence of group allocations will be concealed until after the baseline data collection is completed.

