### Control arm

After randomization, subjects allocated to the control group will receive one 30-min individual session, provided by a coordinator, about the importance of healthy eating and physical activity to prevent type 2 diabetes [4, 22]. The toolkit, including leaflets about healthy eating and instructions for physical activity, is presented to participants in control group. They are instructed to visit a public healthcare center for follow-up, and no additional education is provided.

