### Intensive lifestyle intervention (LSI) core program

The LSI protocol was developed based on the U.S. DPP and a previous literature review related to community-based intervention studies [4, 22]. The major goals of the C-KDPS LSI program are: 1) a minimum of 5–7% loss of initial body weight in 6 months and to maintain this weight loss throughout the study period, 2) increased physical activity of at least 150 min/week with moderate-intensity activity, 3) balanced healthy eating habit, and 4) cessation of smoking and alcohol with stress management. The intensive LSI program is a systematically organized system using web-based program, designed to motivate, empower, and encourage the participants for long-term adherence [23]. Trained C-KDPS coordinators (background in nursing) deliver all the intervention sessions using a web-based system.

The LSI program curriculum is delivered in 18 sessions over 24 weeks (Table 2). During the first 12 weeks, all participants are instructed to visit every week. After one session of orientation, instructions for modifying lifestyle, dietary intake, physical activity, and self-monitoring are introduced for all 18 sessions. During latter 12 weeks, the program focuses on adherence to the LSM. After the 24-week period, personal contact and monitoring are scheduled for at least every 2 months at the public healthcare centers to check adherence to the LSM. The coordinators have the primary responsibility for delivering the LSM program, conducting maintenance sessions, motivating the participants to keep their LSM, assessing the attainment of the goal, and acquisition of required data. All the coordinators are registered nurses, and C-KDPS manuals are provided to minimize the differences among the educators and standardize the intervention contents.

**Table 2 Tab2:** Comparison of core curriculum between DPP and C-KDPS

Session	DPP	C-KDPS
1	Welcome to the lifestyle balance program	Welcome to the C-KDPS program
2	Be a fat detective	How to exercise?
3	Three ways to eat less fat	Reason to lose body weight
4	Healthy eating	Right walking
5	Move those muscles	Healthy eating 1
6	Being activity	Aerobic exercise
7	Tip the calorie balance	Healthy easting 2
8	Take charge of what’s around you	Stretching exercise
9	Problem solving	Food exchange
10.	The four keys to healthy eating out	Aerobic exercise
11	Talk back to negative thoughts	Food exchange
12	The slippery slope of lifestyle change	Whole body Resistance exercise

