### Statistical analysis

The C-KDPS sample size was determined for the primary outcome (between-group difference in diabetes incidence) at 22 months’ follow-up with type 1 error(α) = 0.05 and power (1-β) ≥ 0.80. We aimed to detect a cumulative incidence difference of 11% between the two intervention groups (control group = 19.8% vs. intensive LSI group = 8.6%) based on previous studies [7, 9]. A total of 420 subjects should be recruited, considering the dropout rate of 25% during the study period.

The primary and secondary outcomes will be analyzed using the intention-to-treat approach. Differences in participants’ baseline characteristics and clinical outcomes between two groups were evaluated by a two-sample *t*-test for continuous outcomes and by a Chi-square test or Fisher’s exact test for categorical outcomes. A mixed-model analysis of covariance, including treatment group, gender, age, and the terms and baseline values of clinical parameters, will be used to assess the effects of intervention in a post-intervention survey. For the primary outcome—the comparison of cumulative incidence of diabetes between two groups—a log-rank test with random effects for intercept to account for pre-post correlations within individuals will be used. An interaction effect between time and intervention group will be assessed first. If there is no interaction effect, the overall intervention difference will be assessed. Otherwise, the intervention difference will be assessed at each time point. Adherence to the LSI program is measured by evaluating class attendance, weight loss goal at 6 months, maintenance of physical activity, and achievement of diet goal. For long-term effects of intervention, cost-effectiveness analysis will be analyzed using the Markov model [24].

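### A single fixed block size of 4 within centre-by-sex strata, in a trial that cannot be masked, leaves up to one third of allocations predictable to staff who know the size and keep count

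*Protocol article*

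**What the plan says.** The relevant statements, all in the protocol article, are these.

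- **Randomization:** "The randomization entails measuring the level of the stratified factors—center and sex—for eligible subjects", then "using a block size of 4 within each stratum". Two centres and two sexes give four strata, two at each centre. No second block size is mentioned.
- **Randomization, safeguards:** the procedure "will be conducted by study staff not involved in the intervention through a central computerized process". In addition, "The sequence of group allocations will be concealed until after the baseline data collection is completed".
- **Study design:** "The participants are randomly assigned either to a control group or to an intensive LSI group". The allocation ratio is not stated.
- **Control arm:** "subjects allocated to the control group will receive one 30-min individual session, provided by a coordinator".
- **Intensive lifestyle intervention (LSI) core program:** "Trained C-KDPS coordinators (background in nursing) deliver all the intervention sessions using a web-based system". There are 18 sessions in 24 weeks.
- **Training of coordinator and investigators:** coordinators are taught the study protocol at the initiation meeting.
- **Recruitment:** exclusion 2 removes people judged unable to keep to a lifestyle programme. People whose glucose and HbA1c results are in range are then advised to join.
- **Statistical analysis:** "A total of 420 subjects should be recruited, considering the dropout rate of 25% during the study period".

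**The concern.** One session against eighteen cannot be disguised, so a centre learns each person's arm when treatment begins. With a constant block size, allocations already seen in a stratum determine some of those still to come. Two running tallies per centre, one for men and one for women, are enough to follow this. The two safeguards protect the list itself. They do not touch a prediction that is built from past allocations.

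What is at stake is the comparability of the arms. Motivation and the capacity to adhere are what a lifestyle programme works through, and exclusion 2 is a judgement on just that, made before allocation. If someone with influence over entry expected a given arm, a keen candidate could be brought forward or held back. A resulting difference in motivation would not be repaired by the mixed model in the Statistical analysis section, which adjusts for sex, age and baseline clinical values.

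**Working it through.** **Inputs.** Block size 4; two arms; four strata; total 420 (all from the article). Assumptions: 1:1 allocation; strata of equal size, so 420 / 4 = 105 each.

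**Is 1:1 plausible?** The article gives no predictability figure to reproduce, but its sample size can be checked with equal arms. With pooled variance, two-sided alpha 0.05 and power 0.80, 19.8% against 8.8% (the stated difference of 11 points) needs 158 per arm. Then 158 / 0.75 = 210.7, so 211 per arm and 422 in total, against the stated 420. With the stated 8.6% the result is 152 per arm and 406 in total. Equal allocation therefore fits the plan, and so does an even block size with two arms.

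**Allocations known with certainty, fixed block of 4.** A 2:2 block has 6 equally likely orders.

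- Positions 1 and 2: never determined.
- Position 3: determined when the first two are the same, which is 2 of 6 orders, probability 1/3.
- Position 4: always determined.

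Expected number per block = 0 + 0 + 1/3 + 1 = 1.333. Share = 1.333 / 4 = 33.3%. Applied to the trial, 420 × 1/3 = 140, or about 35 in a stratum of 105.

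**Best-guess accuracy, fixed block of 4.** The best guess is the arm with more places left, or a coin toss if they are equal.

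- Position 1: 1/2.
- Position 2: 2/3.
- Position 3: 1/3 × 1 + 2/3 × 1/2 = 2/3.
- Position 4: 1.

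Mean = (0.500 + 0.667 + 0.667 + 1.000) / 4 = 70.8%.

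**Alternatives.** Fixed sizes were enumerated in the same way. Randomly varying sizes were simulated (2,000 strata of 105, sizes equally likely), with a guesser who knows the set of sizes but not their order.

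| Scheme | Known with certainty | Best guess correct |
|---|---|---|
| Fixed 4 | 33.3% | 70.8% |
| Fixed 6 | 25.0% | 68.3% |
| Fixed 8 | 20.0% | 66.6% |
| Varying 4, 6 | about 5% | about 69% |
| Varying 4, 6, 8 | about 2% | about 68% |

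On 420 participants, about 2% is 420 × 0.02, or about 8 people, against 140 under the fixed size.

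**Imbalance.** The largest difference between arms within an unfinished block is half its size: 4 / 2 = 2 now, and 8 / 2 = 4 with sizes up to 8.

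**The case against.** The strongest reply is that prediction needs three things together, and the article establishes none of them.

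1. *Knowing the block size.* Coordinators are taught the protocol, but the article does not say that this covers randomisation details. It prints the size, yet does not show that it was public while enrolment was open, and enrolment was expected to end by January 2017.
2. *Seeing every allocation in order.* A coordinator learns an arm when a session is given. There may be several coordinators at a centre, and none need see the whole sequence.
3. *Influence over entry.* Database screening lies with a healthcare manager, and randomisation with staff outside the intervention. Who applies exclusion 2 is not stated.

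The room for steering is also limited. Age, BMI, OGTT and HbA1c criteria govern eligibility, with samples sent to a central laboratory. Recruitment is brisk: 420 people in about 26 weeks over four strata is 420 / (26 × 4), or about 4 per stratum per week, roughly one block. Placing a particular person in a particular slot would not be easy.

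These points stand, and they limit the finding to a potential. They do not remove it. The article does not say that the size is withheld, the arms cannot be masked, and the judgement-based entry steps come before allocation.

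A further fair point is that concealment until baseline completion already does most of what a formal lock on eligibility before release would do. No new lock is asked for here.

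**Conclusion.** The point holds as a cheap improvement to the design. A constant block of 4 allows up to one third of allocations, about 140 of 420, to be predicted with certainty. The figure rests on 1:1 allocation and is an upper limit: it applies to someone who knows the size and follows every earlier allocation in the stratum.

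A reader might infer three stronger things that the documents do not support.

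- **That centre staff do know a third of allocations in advance.** For the reasons given under the objection, the article shows only that they could.
- **That selection bias has occurred or can be sized.** The 140 counts predictable allocations; it does not measure an effect on diabetes incidence. What can be said is that such a bias, if it arose, could not be reliably corrected in analysis.
- **That varying the blocks would bring guessing back to 50%.** That is the figure for simple randomisation, which is not proposed. Varying 4, 6 and 8 lowers best-guess accuracy by only about 3 points; its real gain is the loss of certainty.

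The sample size is not affected.

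**What to change.** For all allocations still to be made, generate a new central list with randomly varying block sizes, for example 4, 6 and 8, within the same centre-by-sex strata. Withhold the sizes, and the fact of which are in use, from centre staff. Keep central allocation by staff outside the intervention and the concealment until baseline data collection is complete.

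The cost is one new list and the larger possible imbalance per stratum, 4 instead of 2, which is small against about 105 people per stratum if strata are equal. Using only 4 and 6 holds that maximum at 3 but leaves about 5% of allocations certain. The change cannot help allocations already made; if enrolment has closed, the fixed block size should be acknowledged as a limitation when the trial is reported.

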### Recruitment

Eligible individuals should be in the pre-diabetic range of diabetes: fasting plasma glucose (FPG) 100–125 mg/dL, 2-h post-load plasma glucose (PG) 140–199 mg/dL, or HbA1c 5.7–6.4% (39-46 mmol/mol) [20]. The age and body mass index (BMI) criteria are set at 30 years and older and ≥23 kg/m^2^.

Exclusion criteria are as follows: 1) previous diagnosis of diabetes or diabetes treatment; 2) inability to adhere to lifestyle modification; 3) uncontrolled hypertension or significant ischemic heart disease requiring hospitalization within 6 months of enrollment; 4) either heart failure, anemia (WHO criteria), or cancer requiring treatment in the past 5 years or renal insufficiency; 5) severe liver dysfunction or alcohol abuse; 6) significant arthritis or psychiatric problems; 7) either pregnant or planning to become pregnant; 8) several medications (thiazide, beta blockers, steroid, immune-modulating agents, agents for weight reduction); and 9) other systemic illness affecting the performance of this intervention program.

The screening process is a two-step approach. If the examinees of a national health examination agree to provide their personal information, informed consent is obtained at the time of the health examination. The “healthcare manager” in healthcare centers in Chungju and Suwon city can gain access to the database consisting of the health examination results of the examinees of the habitable areas covered by the healthcare centers. The candidates of this study who are aged ≥30 years, with a BMI ≥ 23 kg/m^2^ are initially screened by fasting glucose level (100-125 mg/dL) from the NHIS database. The C-KDPS program is announced to candidates in both Chungju and Suwon city via brochure or telephone, banner exhibition in the public healthcare centers, and extensive advertisement through the healthcare centers’ web pages.

After initial screening, the participants are instructed to visit their nearby public healthcare centers after overnight fasting. With the informed consent process, the subjects perform a 75-g oral glucose tolerance test (OGTT), HbA1c level, and questionnaires regarding lifestyle habits. Additional blood sampling is done at 30 and 120 min for PG, insulin, and C-peptide levels using the standardized manual of operations [21], and shipped to the central laboratory within 24 h of sample collection. The questionnaires contain self-reported personal data about medical history, employment, education, economic status, smoking or alcohol use, and lifestyle habits including diet and physical activity habits. If the glucose and HbA1c levels of subjects are within the pre-diabetic range, the subjects are recommended to participate in this C-KDPS. In addition, demographic data and a standard 12-lead electrocardiogram are obtained. Anthropometric and laboratory analysis are scheduled to be conducted at baseline, 6, 12, 18, and 22 months.

Recruitment of participants began on July 1, 2016. The enrollment of the participants is expected to be complete by the end of January 2017. Intervention and follow-up of study subjects will be ongoing until December 2018.

